#### Other indicators of treatment efficacy

We will also record the following parameters:

Clearance time (days): The period from enrollment (day 0) to the complete clearance of degenerated and necrotic tendon tissue.

Granulation tissue score: Evaluation of scores at enrollment (day 0), visit 2 (week 2), and at the end of the trial (week 4).

#### Participant timeline {13}

The time schedule of the enrollment, interventions, assessments, and visits for the participants in this trial is shown in Table 1.

**Table 1 Tab1:** Study time-period

	STUDY PERIOD			
	Enrolment	Allocation	Post-allocation	Close-out
TIMEPOINT	-1 day	0 day	After 14 days	After 28 days
ENROLLMENT:				
Eligibility screen	●			
Informed consent	●			
Allocation		●		
INTERVENTIONS:				
Treatment group: Shengji ointment and Pineapple protease (bromelain)		●	●	●
Control group: Comfeel® Plus wound dressing		●	●	●
ASSESSMENTS:				
Demographic data	●			
Medical history and allergy history	●			
Vital signs		●	●	●
Physical examination		●	●	●
Blood routine + C- reactive protein		●		●
Urine routine		●		●
Routine stool + occult blood		●		●
Liver function		●		●
Renal function		●		●
Electrocardiogram		●		●
Urine pregnancy test		●		
Wound coverage rate		●	●	●
Wound healing rate		●	●	●
Amputation extent			●	●
Granulation time			●	●
Maryland Foot Score		●	●	●
Clearance time			●	●
Granulation tissue score		●		●
Adverse events		●	●	●

#### Sample size {14}

The sample size was calculated using Pass 11.0 software (NCSS Statistical software https://www.ncss.com/software/pass). Based on a preliminary review of the literature and the clinical practice and experience of the Second Affiliated Hospital of Tianjin University of Traditional Chinese Medicine in the treatment of diabetic foot ulcers, the control group is expected to have an effectiveness of 50%, and the treatment group of 71%. Postulating a patient ratio of 1:1 between groups and an alpha of 0.05 on both sides, 72 patients would be required in each group. Assuming a 20% loss to follow-up, we calculated a number of 90 patients in each group and a total of 180 patients as the target sample size.

#### Recruitment {15}

The patients will be followed up at four hospitals; the Second Affiliated Hospital of Tianjin University of Traditional Chinese Medicine (80 patients), Affiliated Hospital of Liaoning University of Traditional Chinese Medicine (40 patients), Affiliated Hospital of Shanxi University of Traditional Chinese Medicine (40 patients), and Tianjin Binhai New Area Hospital of Traditional Chinese Medicine (20 patients).

Assignment of interventions: random allocation.

#### Sequence generation {16a}

Using a central random system and minimization algorithm, the allocation probability of the target group will be calculated for each enrolled patient for them to be assigned to the most suitable treatment group and ensuring a balance of control factors between the groups. The controlling factors are (1) ulcer location (plantar, dorsum of foot, or toe), and (2) ABI evaluation index (> 0.7, and ≤ 0.7).

#### Concealment mechanism {16b}

None.

### Data collection and management

#### Data management {19}

Research medical records.

Since most outpatient medical records at China’s hospitals are kept by the patients themselves, the case report form will be designed specifically for this trial to preserve first-hand information. The research medical records are the original documents of the trial patients, which are properly kept by each trial center.

2Electronic data management.

The electronic case report form is created using the clinical trial data management system (eCDMS3.0) at Xiyuan Hospital developed by the Chinese Academy of Traditional Chinese Medicine, and the data will be collected and managed online.

Full analysis set: This refers to patients receiving the allocated treatment at least once and having data on at least one post-treatment primary outcome measurement. For patient data that fail to observe the whole treatment process, the data from the last observation will be carried forward to the final last observation carried forward.Per protocol set: Good compliance (80% ≤ treatment compliance ≤ 120%), not taking prohibited medications during the study, and no serious violation of the trial protocol.Safety set: All patients who are randomized and use the trial treatment at least once.

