### Trial design {8}

This study was a multicenter, non-blind, randomized, positive control trial.

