##### Patients who voluntarily withdraw from the trial

Every patient has the right to withdraw from the trial in accordance with the Good Clinical Practice (GCP) and informed consent. “Withdrawal” also refers to the loss of a patient after he/she no longer receives the treatment and assessment of the intervention, although he/she does not explicitly propose withdrawal from the study.

If the intervention or control is found to be ineffective, the patient may be unwilling to continue the trial. If the patient proposes to withdraw from the trial to the researcher before returning to the routine treatment.Patients who, due to various other reasons, are unwilling or unable to continue the clinical trial and terminate the trial by offering to withdraw from the trial to the researcher.Although the patients do not explicitly propose withdrawing from the study, they are no longer followed up and are thus lost.

Researchers will aim to learn as much as possible about the reasons for patients’ withdrawal and record them. For example, the perceived curative effect may not be good; patients may not tolerate some adverse reactions; patients may be unable to continue the clinical trial for various reasons, e.g., economic factors; or loss of follow-up without explanation.

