### Statistical methods for primary and secondary outcomes {20a}

Statistical description.Detailed description of cases of withdrawal and censoring, including the time and reason for censoring.Descriptive statistics: Based on their distribution, data will be presented as either the mean and standard deviation, or the median with maximum, minimum, and confidence interval, or the number and frequency (%), among others.Statistical inference method.Measurement data: The paired t-test, analysis of variance, the rank-sum test, signed rank-sum test, and the median test will be used.Counting data: The chi-square test, Fisher exact test, and others will be used; grade data will be analyzed using the ridit test and the Cochran–Mantel–Haenszel test.Primary outcome analysis: Per protocol set analysis and full analysis set analysis will be performed. The Cochran-Mantel-Haenszel test will be used for multicenter counts and analysis of covariance for measures. For the confounding factors that are difficult to control or are uncontrolled before allocation, the least-squares means of the analysis of covariance and their 95% confidence limit or logistic regression will be used as covariates to determine the between-group efficacy.Two-sided difference tests will be used to assess statistical differences, and a difference with a p-value of ≤ 0.05 will be considered to be statistically significant.

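### The full analysis set omits patients with no post-treatment coverage measurement and fills later gaps by LOCF, which can bias the primary comparison by an amount and in a direction the protocol does not determine

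*Protocol article*

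**What the plan says.** The analysis sets are in the protocol article under Data management {19}. Membership of the full analysis set needs both treatment and an outcome: "This refers to patients receiving the allocated treatment at least once and having data on at least one post-treatment primary outcome measurement". For patients who do not complete the course, "the data from the last observation will be carried forward to the final last observation carried forward". The per-protocol set requires compliance between 80% and 120%, and also "not taking prohibited medications during the study, and no serious violation of the trial protocol".

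Under Statistical methods {20a}, the primary outcome entry says "Per protocol set analysis and full analysis set analysis will be performed", and the same section says "Two-sided difference tests will be used to assess statistical differences". Trial design {8} reads "This study was a multicenter, non-blind, randomized, positive control trial".

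Table 1 schedules wound coverage at day 0, after 14 days and after 28 days. Sample size {14} allows for 20% loss. On voluntary withdrawal the protocol says "If the intervention or control is found to be ineffective, the patient may be unwilling to continue the trial". Researchers may also withdraw patients who reach a clinical endpoint such as the need for surgery, and patients whose glucose is not normalised within a week are discontinued. The section on researcher-decided termination gives withdrawn subjects a final visit at which the efficacy indicators are assessed.

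**The concern.** Two stated rules act on the same patients. A patient who leaves before any post-treatment measurement is removed from the full set, so membership depends on what happens after randomisation. A patient who leaves later has an earlier coverage value counted as the day-28 value. The Abstract describes granulation tissue as growing and merging under treatment, so assuming no change after the last scan is hard to defend.

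Neither rule would matter much if loss were small and unrelated to outcome. Here one patient in five is expected to be lost, patients know their arm, and the protocol itself names perceived ineffectiveness and clinical endpoints as routes out. Who leaves, when and why may therefore differ by arm. At stake is whether the primary test keeps its 5% error rate and whether the estimated difference is that of the randomised groups.

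**Working it through.** **The plan's own figure.** From "an alpha of 0.05 on both sides, 72 patients would be required in each group" and 20% loss, 72/(1 - 0.20) = 90 per group, or 180 in total. This reproduces. The inflation protects the number analysed. It does not protect the comparability of those who remain.

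**Inputs.** From the document: 90 per arm, 20% overall loss, coverage scans at days 14 and 28, and a two-sided test at 0.05. Assumed, because the document gives no figure:
- loss of 15% in one arm and 25% in the other (average 20%);
- average coverage growth G from day 14 to day 28 of 20 to 40 points;
- SD of coverage around each visit mean of 25 to 35 points;
- the fraction f of average growth that leavers would have gained had they stayed, either 0.25 or 1.

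**LOCF, with no true effect and all loss after day 14.**

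Bias = (0.25 - 0.15) × f × G, in favour of the arm with less loss.
- f = 1: 0.10 × 20 = 2 points up to 0.10 × 40 = 4 points.
- f = 0.25: 0.5 to 1.0 point.

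Carrying day-14 values forward mixes two visit means, which adds d(1 - d)G² to the variance of an arm with loss d. For f = 1:

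SE = √{[2·SD² + (0.15×0.85 + 0.25×0.75)·G²]/90} = √{[2·SD² + 0.315·G²]/90}

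Type I error = P(|Z + bias/SE| > 1.96).

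| f | G | SD | Bias | SE | Type I error |
|---|---|---|---|---|---|
| 1 | 20 | 35 | 2 | √(2576/90) = 5.35 | 6.6% |
| 1 | 40 | 25 | 4 | √(1754/90) = 4.41 | 14.8% |
| 0.25 | 20 | 35 | 0.5 | 35√(2/90) = 5.22 | 5.1% |
| 0.25 | 40 | 25 | 1.0 | 25√(2/90) = 3.73 | 5.8% |

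The f = 0.25 rows use the simple SE. The mixing variance only lowers them slightly, so they stay at about 5-6%.

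**Exclusion, with no true effect and all loss before any measurement.** The sample size is framed as an effectiveness rate, so this check uses a responder scale: 50% true response in both arms, and every lost patient a non-responder (an extreme assumption). The observed rate is 0.50/(1 - d).
- Loss 20% and 20%: 62.5% versus 62.5%, type I error 5%.
- Loss 15% and 25%: 0.50/0.85 = 58.8% versus 0.50/0.75 = 66.7%. This is a spurious 7.8 points in favour of the arm with more loss, with a type I error of about 16%.

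Counting all 90 per arm, with the losses as failures, restores 50% versus 50% in this scenario.

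**Direction.** With the same 15%/25% split, LOCF favours the arm with less loss, while exclusion of failures favours the arm with more. The net direction depends on timing, reasons and arm, none of which the document gives.

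**The case against.** The strongest reply is the final visit. A patient withdrawn before day 14 can still supply a coverage value and enter the full set, and a later leaver carries forward the withdrawal-visit value rather than the day-14 value. That stands, and it softens both mechanisms. But the visit is written under researcher-decided termination, and whether it covers voluntary leavers is not said. It cannot reach patients lost without contact. Even when it takes place, an early value is carried forward as the day-28 result.

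It is also fair to say that patients who leave because they see no effect would probably have gained less than average, which shrinks the LOCF bias. This is why the f = 0.25 rows are shown. Exclusion completely at random does not bias at all, even with unequal rates.

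Three stronger readings are tempting, and the documents support none of them.
- A reader might infer that the bias favours Shengji ointment with bromelain. That needs a particular pattern of loss by arm, and no section gives one.
- A reader might infer that the full and per-protocol sets are co-primary, so that success on either would count. The text says only that both analyses will be done. It states no such decision rule, and the ranking may be in an analysis plan not shown.
- A reader might quote much larger error rates, such as 19% at a 15%/25% split or 57% at 10%/30%. These give leavers the full average growth and ignore the variance that LOCF adds. With that variance the same cases are 14.8% and 44.6%, and with a quarter of the growth they are below 6% and about 8%.

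**Conclusion.** The concern holds in a limited form. The article itself fixes an outcome-dependent full analysis set and LOCF, in a non-blind difference trial that plans 20% loss and foresees outcome-related withdrawal. This can bias the primary comparison. The final visit reduces the problem without removing it.

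The size cannot be read from the document. With assumed loss after day 14 of 15% versus 25%, growth of 20-40 points and SD of 25-35, the LOCF part gives a type I error of about 5-6% (leavers gain a quarter of the average growth) to about 7-15% (they gain all of it). The exclusion part reaches about 16% only under the extreme assumption that every unmeasured patient failed. Equal loss of the same kind in both arms leaves the error at 5%.

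**What to change.** 1. Make the primary analysis all randomised patients in their allocated arm.
2. Replace LOCF by multiple imputation of day-28 coverage from baseline coverage, any post-baseline coverage including the withdrawal visit at its actual date, arm, and the minimisation factors (ulcer location and ankle-brachial index). A mixed model on days 14 and 28 is not enough alone: it adds no outcome information for patients with no post-baseline scan. Use it only with baseline included and those patients covered by imputation.
3. Add a delta-adjusted or worst-case sensitivity analysis, since leaving for lack of effect makes missing-at-random doubtful.
4. State that this analysis decides and that the per-protocol analysis is supportive.

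The cost is a little more programming and a dated amendment, with no new data. Trial status expected recruitment to end in December 2022, so timing matters in a non-blind trial. The change should be dated before comparative data are analysed. If they have already been analysed, report the new analysis alongside the planned one and label it post hoc.

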##### Treatment 1: Shengji ointment

Size: 30 g/box.Formulation: Ointment.Usage and dosage: For external use. The ointment will be spread on skimmed cotton and applied to the affected area.Route of administration: Topical.Frequency of administration: Once every 24 h.Treatment course: Four weeks.Manufacturer: Tianjin Darentang Jingwanhong Pharmaceutical Co., Ltd, Tianjin, Tianjin, China.

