##### Active control: Comfeel® Plus wound dressing

Size: 25 g/piece.Formulation: Hydrocolloid dressing.Usage and dosage: Apply Comfeel® dressing to the ulcer. Ensure the dressing height is at the level of the surrounding skin. Then, apply a layer of dressing over the ulcer and surrounding area.Manufacturer: Coloplast Group, Humblebaek, Denmark.Route of administration: Topical.Frequency of administration: Once every 24 h.Course of treatment: Four weeks.

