##### I. Termination of a patient’s participation based on the researcher’s decision

The researchers may decide to withdraw enrolled subjects from the study when they establish that they are not suitable to continue the study for any of the following reasons:

During the trial, clinical endpoints (such as the need for surgery) are reached.The patient undergoes surgical treatment other than debridement of the ulcer site.During the clinical trial, patients experience complications or physiological changes that make it inappropriate for them to continue to receive treatment within the trial.Use of other prohibited treatments or drugs that affect the assessment of the efficacy and safety of the intervention.If serious adverse events occur during the trial, the researcher may decide whether to suspend the trial.Poor compliance of the patients that results in the failure of 80% of the prescribed dosage of topical drugs (except cured patients) or the failure of 120% of the prescribed dosage.

Subjects who will be withdrawn from the trial will undergo a final visit to evaluate each efficacy indicator and to complete a safety assessment.

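### Cured patients are exempt from the 80% compliance floor for withdrawal but not in the per-protocol definition, so early-cured patients can be dropped from the per-protocol analysis because of their outcome

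*Protocol article*

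**What the plan says.** Four parts of the protocol article bear on this.

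- **Withdrawal, section I under {11b}.** Researchers may withdraw a patient for poor compliance, described as "failure of 80% of the prescribed dosage of topical drugs (except cured patients) or the failure of 120% of the prescribed dosage". Cured patients are expressly excepted from the lower limit.
- **Analysis sets, Data management {19}.** The per-protocol set requires "Good compliance (80% ≤ treatment compliance ≤ 120" (per cent), together with conditions on prohibited medication and serious violations. The limits are the same and no exception is stated. The denominator of compliance is not defined.
- **Interventions {11a}.** Shengji ointment is given as "Frequency of administration: Once every 24 h.Treatment course: Four weeks", bromelain on the same schedule, and the hydrocolloid control as "Frequency of administration: Once every 24 h.Course of treatment: Four weeks". Both arms therefore have the same nominal course.
- **Statistical methods {20a}.** For the primary outcome, "Per protocol set analysis and full analysis set analysis will be performed". Neither set is named as the leading one.

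**The concern.** The withdrawal rule shows that its authors foresaw patients who fall below 80% because the wound is cured and treatment stops, and who should not be treated as poor compliers. The per-protocol definition reuses the limits but not that exception. The same patient, with the same applications, is then acceptable under one rule and non-compliant under the other.

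What is at stake is the meaning of the per-protocol comparison. A patient would leave it because of an outcome reached after randomisation, not because treatment was taken badly. The two arms can lose different numbers of such patients, and the patients lost differ systematically from those who stay. The trial is also non-blind. If the rule is left open, someone who knows the allocation may have to decide case by case whether a cured patient was compliant.

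**Working it through.** **1. The threshold.** Once every 24 h for four weeks gives 4 × 7 = 28 applications. The floor is 0.80 × 28 = 22.4.

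- 22 applications: 22/28 = 78.6%, fails.
- 23 applications: 23/28 = 82.1%, passes.

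A patient who stops at cure after 22 or fewer applications fails the per-protocol criterion. If days 0 and 28 both carry an application, 29 are due, the floor is 0.80 × 29 = 23.2, and 24 are needed. The problem is the same, one application later.

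**2. Which denominator is meant.** There are two candidates.

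- *Full course.* A cured patient who stops early falls below 80%, and the exception in the withdrawal rule has work to do.
- *Applications due until cure.* Stopping at cure cannot lower compliance, and the exception would be needless.

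The exception therefore favours the full-course reading, and under that reading the per-protocol definition excludes early-cured patients.

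**3. Direction, using the protocol's planning rates.** Inputs from Sample size {14}: effectiveness 50% in control and 71% in treatment. Assumptions of this review: a share c of control and t of treatment patients are cured after 22 or fewer applications, all of them count as effective, and all are dropped from the per-protocol set. The rates that remain are (0.50 − c)/(1 − c) and (0.71 − t)/(1 − t), so the per-protocol difference is

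D = 0.50/(1 − c) − 0.29/(1 − t).

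| Early cure, control (c) | Early cure, treatment (t) | D (points) |
|---|---|---|
| 0% | 0% | 21.0 |
| 5% | 5% | 22.1 |
| 10% | 10% | 23.3 |
| 5% | 10% | 20.4 |
| 5% | 15% | 18.5 |
| 10% | 20% | 19.3 |

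With c = 5%, D equals 21.0 when 1 − t = 0.29/(0.5263 − 0.21) = 0.917, that is t = 8.3%. Below that the difference is inflated, and above it the difference is diluted.

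Starting from 72 per arm, power (two-sided 0.05, pooled test) is 73.6% with nobody dropped. Over the rows above it runs from 56.5% (5% v 15%) to 76.9% (10% v 10%). These figures include the loss of patients as well as the change in D.

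**4. Direction, using a continuous measure.** Take the wound healing rate with cured = 100 and assumed means of 60 (treatment) and 50 (control) in uncured patients. The true difference is 10 + 40t − 50c, and without cured patients it is 10.

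- t = 20%, c = 10%: 10 + 8 − 5 = 13.0 becomes 10.0 (diluted).
- t = 10%, c = 9%: 10 + 4 − 4.5 = 9.5 becomes 10.0 (inflated, although treatment cures more patients early).

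**5. Limits of these illustrations.** The per-protocol analysis is specified for the primary outcome, granulation coverage. The wound healing rate is a secondary outcome, and the planning section does not tie effectiveness to coverage. On coverage itself a closed wound has no clear value: with the current wound area as denominator it is 0/0, and with the original area it could score 0%. Steps 3 and 4 therefore show that the direction is not fixed. They do not give the size of the effect on the primary analysis.

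**The case against.** The strongest reply is that the two rules do not strictly contradict each other. One is a discretionary withdrawal rule about prescribed dosage. The other is a one-line set definition using treatment compliance with no stated denominator. If compliance is counted only up to cure, no cured patient is lost, and a fuller document not shown here may say so. This stands in part: exclusion follows from the full-course reading, not from the definition alone. But the protocol does state a numeric definition, and its own withdrawal rule points to the full-course reading, so the two need to be reconciled.

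A second reply is that few patients are affected. This stands. The ulcers are Wagner grade 3–4 with exposed tendon, cure would have to come within about 22 daily applications, and the document gives no rates.

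A reader might also infer two stronger conclusions that the document does not support.

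- *That the per-protocol estimate is necessarily pulled towards no difference.* It is not. Equal early cure inflates the difference in step 3, and in step 4 so does a slightly higher early-cure rate on treatment.
- *That any disagreement with the full analysis set would be an artefact of this rule.* The two sets also differ on prohibited medication and serious violations, and the full analysis set carries the last observation forward.

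**Conclusion.** The inconsistency is real and worth correcting before the per-protocol set is fixed. As written, and counted against 28 applications, a patient of either arm cured after 22 or fewer is retained in the trial but excluded from one of the two analyses of the primary outcome. That exclusion depends on the outcome.

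The size and direction of any bias are unknown. They depend on early-cure rates in each arm, which the document does not give, and on how a closed wound is scored for coverage. With the assumed rates in step 3, the planning difference of 21.0 points ranges from 18.5 to 23.3. The full analysis set does not use the compliance limits and is unaffected, so this does not undermine the trial's result as a whole.

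**What to change.** Reconcile the per-protocol definition in Data management {19} with the exception already made in section I under {11b}. Add one sentence to the definition: for a patient classed as cured, compliance is the number of applications made divided by the number due up to the date of cure, and applications not made afterwards do not count against the patient. For all other patients, state the denominator for the full course, so that it is clear whether 28 or 29 applications are due. The withdrawal rule itself needs no change.

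The costs are small.

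- The date of cure must be recorded. It is not among the listed outcomes or the items of Table 1, and the case report form is not shown.
- What counts as cured is not defined in the article, so the definition has to be stated and used consistently.
- The per-protocol set will contain some patients with fewer than 23 applications, which should be reported.

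Because the trial is non-blind, the sentence should be fixed before anyone assigns patients to the set.
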